### 2.2. Design

We designed a pragmatic multicentre RCT with three study arms and stratified random allocation. Participants in the WLC group receive care from the treatment centre as usual, and participants in the intervention groups also have access to the usual care in addition to participating in the 6-week iEFT or iMMI programme. Although both interventions require patient engagement, the “live attendance” is organised differently: the intervention format of the iMMI programme includes six weekly 2-h sessions, while the duration of the three individually guided iEFT sessions varies. A first iEFT session lasts about 90 min, the second 45 min, and a third 25 min. Time toxicity is included as one of the objectives (i.e., time spent per patient). The study evaluation will be done by comparing the within-group and between-group differences. The potential effect will be assessed over time on a series of patient-reported outcome measures (PROMs). Measurements will take place at baseline (T0; before randomisation), 6 weeks (T1; 6 weeks after T0 for the WLC and 6 weeks after the first iEFT or iMMI session for the intervention groups); 12 weeks (T2; 12 weeks after T0 for the WLC and 12 weeks after the first iEFT or 6 weeks after the last iMMI session for the intervention groups); 24 weeks (T3; 24 weeks after T0 for the WLC and 12 weeks after the last iEFT or iMMI session for the intervention groups). Participants are allowed to withdraw at any time. There will be no follow-up assessments of these drop-outs. The development of the study protocol followed the SPIRIT (Standard Protocol Items: Recommendations for Interventional Trials) guidelines [25]. The planned flow diagram of the REMOTE trial is presented in Figure 1. The protocol is reported according to the SPIRIT guidelines (Supplementary Materials Section SA: Table S1).

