### 2.5. Sample Size Calculation

The sample size calculation takes into account the principle of minimization for randomization, with participants randomized into either the iEFT group, iMMI group, or WLC group. In order to achieve at least 80% power to detect a between-group difference in mean FCRI at T1 of 10 points using an independent samples *t*-test at the two-sided 2.5% significance level (two experimental groups are compared against a single control), a total sample size of 444 patients (148 in each group) is needed, assuming a common standard deviation for FCRI in all groups of 27.9 points.

When taking into account baseline FCRI as a covariate in the regression model, the calculated sample size can be reduced by a design factor equal to (1 – r^2^) [28]. Assuming a correlation between baseline and follow-up FCRI of 0.6, the sample size reduces to 288 patients in total. This sample size has been increased to 339 patients in total to allow for an expected drop-out rate of 15%. This means we will include 113 patients in each group: iEFT (intervention), iMMI (active control), and the WLC group.

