### 2.10. Data Analysis

All planned analyses will be performed according to the intention-to-treat principle.

Descriptive statistics will be used to describe demographic and clinical characteristics.

Clinical and psychosocial outcomes will be compared between groups using linear mixed models. Linear mixed-effects models will assess whether the improvement in FCRI scores and secondary PROMs is significantly different over time. Models will explore time x group as an interaction effect and will include the stratification variables (age, chemotherapy, and gender). Estimated marginal means with 95% confidence interval (CI) will be calculated for each time point for both groups. A 5% significance level will be used.

Within-group differences will be calculated by pairwise comparisons, enabling us to detect differences over time within the three groups. Between-group differences in the primary outcome at the primary endpoint T1 will be further examined with pairwise comparisons with T0 as the reference time point. These analyses will be repeated for the secondary PROMS: distress, QoL, and health status.

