## 4. Discussion

The aim of this study is to examine the efficacy of iEFT and iMMI in alleviating FCR, one of the most frequently reported psychosocial problems by cancer survivors. Based on the outcomes of the former EMOTICON trial [32], it is expected that iEFT may control and diminish FCR experienced by cancer survivors. The integration of exposure therapy, cognitive framing, and acupressure [15] renders EFT a straightforward yet effective tool to manage negative thoughts. Furthermore, it is a patient-friendly intervention that can be easily delivered remotely.

For the active control arm in the study, iMMI, it is expected that this intervention arm will also be able to reduce FCR. In addition, this intervention group may offer novel insights into the impact of this particular mindfulness approach on FCR and on the overall psychological well-being of cancer survivors.

One of the potential limitations related to the type of intervention and topic of the trial assumes a potential selection bias for white, highly educated, female participants. However, the research group consciously decided to include all cancer types as all cancer survivors may cope with (severe) levels of FCR. We have anticipated by including the biggest risk factors for selection bias (age, gender), which are also related to higher levels of FCR, as stratification variables. Hereby, the intervention arms should all contain equal distribution of younger/older and male/female participants. Race and ethnicity are not taken into consideration, and this may potentially be a topic for the final discussion together with the general analysis of the demographic data.

Another limitation could be the entire online format, which increases the risk for drop-out. We may anticipate this by keeping close contact with local trial coordinators in the first place, stressing the importance of the eligibility criteria, but even more the importance of the motivation of participants. Next, it is the central coordinator’s responsibility to follow up on all participants and the response to the online questionnaires via MyNexuzHealth.

Positive outcomes may promote the integration of iEFT and iMMI into clinical practice. Therefore, the time toxicity of both interventions is measured as this may significantly impact the feasibility of implementation.

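### Assessments end for everyone who drops out, without separating stopping the programme from withdrawing consent to data collection; this weakens the intention-to-treat comparison at T1

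*Protocol article*

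**What the plan says.** Section 2.2 (Design) of the protocol article permits withdrawal at any point and then states the rule: "There will be no follow-up assessments of these drop-outs". No section defines a drop-out, and none separates leaving the programme from declining further questionnaires.

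Section 2.10 (Data Analysis) commits to intention-to-treat: "All planned analyses will be performed according to the intention-to-treat principle". It names the model: "Clinical and psychosocial outcomes will be compared between groups using linear mixed models".

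Section 2.5 (Sample Size Calculation) uses one overall loss rate: "This sample size has been increased to 339 patients in total to allow for an expected drop-out rate of 15" per cent. It gives no arm-specific rate.

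The Discussion (section 4) names a risk: "Another limitation could be the entire online format, which increases the risk for drop-out". The same paragraph makes the central coordinator responsible for following up all participants and their online questionnaire responses. Section 2.7.3 offers the wait-list a programme only after the T2 assessment.

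**The concern.** An intention-to-treat comparison needs the T1 FCRI of randomised participants whether or not they kept attending. The rule in section 2.2 can be read as ending data collection for anyone who stops the sessions. The programmes last six weeks, and T1 falls six weeks after the first session, so stopping early normally happens before T1. Such a participant then has T0 and the stratification variables only, and the mixed model has to predict T1 from comparable people in the same arm who stayed.

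The prediction is weak. At the protocol's assumed correlation of 0.6, baseline explains 36% of the variance of the T1 score. If people leave because the sessions do not help, their true T1 scores are worse than predicted and the programme looks better than it is. An analysis plan can choose how to model missing scores, but it cannot recover scores that were never collected.

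**Working it through.** **Inputs from section 2.5:** difference 10 points, SD 27.9, two-sided 2.5% per comparison, power 80%, correlation 0.6, drop-out 15%, 113 per arm.

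**Reproducing the plan's sample size**
- Unadjusted: n = 2 × (2.241 + 0.842)² × 27.9² / 10² = 148 per arm, 444 in total, as stated. An exact t-test calculation gives 150 per arm, 450 in total.
- Baseline adjustment: 148 × (1 − 0.6²) = 94.7, so 95 per arm and 285 in total; from 150 it is 150 × 0.64 = 96 per arm, or 288. The stated 288 is reproduced within rounding.
- Drop-out: 96 / 0.85 = 112.9, so 113 per arm and 339 in total, as stated.

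The inflation is therefore correct. It plans for 339 − 288 = 51 participants (17 per arm) without outcomes. It protects power and does nothing about bias.

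**Power**
The adjusted SD is 27.9 × √0.64 = 22.32. Power = Φ(10 / SE − 2.241), with SE = 22.32 × √(2/n).
- n = 96: SE = 3.22, power 80.6%.
- n = 113: SE = 2.97, power 87.0%.

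**Bias in the contrast**
Let d be the drop-out share in an arm. Let D be the amount by which drop-outs' true mean T1 FCRI exceeds what the model predicts for them. Then:

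bias = d(programme) × D(programme) − d(wait-list) × D(wait-list)

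The documents give neither arm-specific d nor D, so the values below are assumptions. Each row keeps the overall rate at the planned 15%: (20 + 20 + 5)/3 = 15 and (22.5 + 22.5 + 0)/3 = 15. The same D is used in both arms.

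| Drop-out, programme vs wait-list | D = 5 | D = 10 | D = 15 |
|---|---|---|---|
| 15% vs 15% | 0 | 0 | 0 |
| 20% vs 5% | 0.75 | 1.5 | 2.25 |
| 22.5% vs 0% | 1.1 | 2.3 | 3.4 |

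For example, 0.20 × 10 − 0.05 × 10 = 1.5. Against the 10-point target, the unequal rows run from about 8% to 34%. Equal drop-out removes the bias only if D is also equal; otherwise 0.15 × (D(programme) − D(wait-list)) remains.

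**Enrolment:** section 3 reports 82 of 339 at 31 July 2025, leaving 339 − 82 = 257 still to come.

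**The case against.** The two sentences in section 2.2 belong together: the drop-outs are those who withdraw. If withdrawing means leaving the study, ending assessments is unavoidable, and the coordinator's duty in section 4 to follow up everyone supports that reading. This stands as a possible reading. The article does not say it is the intended one, however, and the Discussion ties drop-out to the online format rather than to consent.

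Three stronger conclusions are tempting, and the documents do not support them.

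- *A reader might infer that the rule contradicts intention-to-treat.* It does not. Drop-outs can still be analysed as randomised, and the mixed model uses what was observed under a missing-at-random assumption. The rule makes the analysis lean harder on that assumption.
- *A reader might infer that outcomes are removed selectively from the programme arms.* The rule is written for all participants, and section 2.5 has a single rate. Unequal loss is a reasonable inference, because only the programme arms have sessions to leave and the wait-list gains a programme by staying to T2. It is not a stated fact.
- *A reader might multiply the planned 15% by a 10-point gap and set the resulting 1.5 points against the 10-point target.* That product is the bias in one arm's mean. In the contrast it cancels if drop-out and gap are the same in both arms.

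The direction is not certain either, since some people may stop because they feel better. The consent form and the supplementary list of collected variables are not shown and may already draw the distinction.

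**Conclusion.** The point holds as a badly fixed rule and should be corrected. Section 2.2 states affirmatively that assessments end, and nothing in the article limits this to people who refuse further data collection. Applied to people who stop the sessions, it gives up T1 scores that could have been obtained, and it fits poorly with the follow-up of all participants described in section 4.

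The size is conditional. Bias in the contrast is 0 if drop-out and unexplained gap match across arms, and about 0.75 to 3.4 points in the unequal scenarios. These rest on assumed arm-specific rates and an assumed gap of 5 to 15 points beyond what observed data explain. The likely direction favours the programmes. If all outcomes were retained, power would rise from about 80.6% to 87.0%; this is an upper limit, because some participants will withdraw consent. Severity: should-fix.

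**What to change.** Replace the sentence in section 2.2 with wording such as: *Participants who stop the programme remain in the study and are asked to complete T1, T2 and T3; assessments stop only if the participant withdraws consent to data collection.* Record programme discontinuation and study withdrawal as separate items in REDCap, with dates, unless the case report form already does so.

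The cost is a short protocol amendment across the twelve sites, possibly one extra data field, and a few more reminders. The questionnaires are already online and centrally followed up. The change would help the 257 participants not yet enrolled at 31 July 2025 and those still in follow-up. It cannot recover assessments already missed.

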### 2.3. Eligibility Criteria

The eligibility criteria are listed in Table 2.

### 2.4. Setting and Recruitment Process

The recruitment takes place in twelve hospitals located throughout Flanders and Brussels, Belgium (Supplementary Materials Section SB: Table S2). Patients coping with FCR are identified by their treating oncologists or another healthcare professional involved throughout their disease trajectory. They can also be recruited through publicity, such as flyers in waiting rooms or projections on screens in the oncology units. Participation in the trial is also discussed with the healthcare professional (medical oncologist, GP, or psychologist), and this is explicitly mentioned in the ICF.

Potential candidates will receive a general outline of the study. When interested in participation, the assigned PI or his/her designee will complete the informed consent form (ICF) and screening procedure with the Cancer Worry Scale (CWS) 6-item version [26] (Appendix A). When eligible for participation (i.e., score of 10 or higher on the CWS; see Table 2), the local PI or his/her designee completes the electronic Case Report Form (eCRF), followed by the QuAno form (Quest Anonymous by NexuzHealth; nexuzhealth NV, Hasselt, Belgium) and allocates the participant to one of the three groups in REDCap (Vanderbilt, Nashville, TN) [27]. Upon completion of the local procedure, the central project coordinator ([name], [name], [name]) from the coordinating site az groeninge (Kortrijk, Belgium), follows up on the inclusion. It’s the central project coordinator’s responsibility to contact each participant by phone to explain further details regarding study participation and address any questions.

### 2.5. Sample Size Calculation

The sample size calculation takes into account the principle of minimization for randomization, with participants randomized into either the iEFT group, iMMI group, or WLC group. In order to achieve at least 80% power to detect a between-group difference in mean FCRI at T1 of 10 points using an independent samples *t*-test at the two-sided 2.5% significance level (two experimental groups are compared against a single control), a total sample size of 444 patients (148 in each group) is needed, assuming a common standard deviation for FCRI in all groups of 27.9 points.

When taking into account baseline FCRI as a covariate in the regression model, the calculated sample size can be reduced by a design factor equal to (1 – r^2^) [28]. Assuming a correlation between baseline and follow-up FCRI of 0.6, the sample size reduces to 288 patients in total. This sample size has been increased to 339 patients in total to allow for an expected drop-out rate of 15%. This means we will include 113 patients in each group: iEFT (intervention), iMMI (active control), and the WLC group.

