## 2. Methods/Design

### 2.1. Aim and Objectives

The primary aim of this study is to examine whether two different interventions (iEFT and iMMI) can improve FCR experienced by cancer survivors, compared to a usual care wait-list control (WLC) group. To translate a statistically significant effect on FCR into a clinically significant change, we would need to detect a between-group difference in mean FCRI at T1 of 10 points (with T1 6 weeks after participation in the iEFT or iMMI programme, or 6 weeks waiting list; see Figure 1).

The secondary and tertiary objectives are listed in Table 1.

Our hypotheses are:iEFT improves FCR compared to the WLC group at T1iMMI (active control intervention) improves FCR compared to the WLC group at T1

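### Sections 2.5 and 2.10 give two significance levels and no decision rule for the two primary contrasts; naming Holm would fit both at no cost in sample size

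*Protocol article*

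**What the plan says.** Section 2.1 gives the aim, to "examine whether two different interventions (iEFT and iMMI) can improve FCR experienced by cancer survivors" compared with the wait-list, and lists one hypothesis for each programme at T1. Section 2.9 names both contrasts as primary.

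Section 2.5 plans for "at least 80% power to detect a between-group difference in mean FCRI at T1 of 10 points", "at the two-sided 2.5% significance level (two experimental groups are compared against a single control"). The other inputs are "assuming a common standard deviation for FCRI in all groups of 27.9 points", the result that "a total sample size of 444 patients (148 in each group) is needed", and then "Assuming a correlation between baseline and follow-up FCRI of 0.6, the sample size reduces to 288 patients in total". An allowance for 15% drop-out brings the total to 339, or 113 per arm.

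Section 2.10 describes linear mixed models and pairwise comparisons and adds "A 5% significance level will be used". It does not mention the 2.5% level, a split, a step-down or a family-wise error rate.

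**The concern.** The article gives one level for planning and another for analysis, with no rule to link them. Two literal readings are open, and each has a price.

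- **2.5% for each contrast.** This is a valid Bonferroni split. However, a second contrast with p between 0.025 and 0.05 would be called negative even when the first has clearly succeeded. Holm removes that loss, controls the same family-wise error with no further assumptions, and rejects whatever the split rejects.
- **5% for each contrast.** Two chances at 5% are taken, so the family-wise error exceeds 5%.

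The Discussion (Section 4) expects both programmes to reduce fear of recurrence, and the abstract foresees implementing either or both. A separate verdict on each programme is therefore what readers will want, and the rule decides how the second one is reached.

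**Working it through.** **Inputs (Sections 2.5 and 2.6).** Difference 10 points; SD 27.9; baseline to follow-up correlation 0.6; two-sided 2.5% per contrast; 80% power; 15% drop-out; allocation 1:1:1.

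**1. The plan's own figures.** The normal-approximation formula is n per arm = 2 × (SD/difference)² × (z₀.₉₈₇₅ + z₀.₈₀)².
- 2 × 2.79² × (2.241 + 0.842)² = 147.98, so 148 per arm and 444 in total, as stated. An exact t-test needs 149.2, so 150.
- The covariate factor is 1 − 0.6² = 0.64. 444 × 0.64 = 284.2 against the stated 288; 150 × 0.64 = 96 per arm gives 288 exactly.
- 288 / 0.85 = 338.8, so 339.

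The sample size is reproduced, and it rests on 2.5% per contrast.

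**2. Set-up for the joint calculation.**
- Adjusted SD = 27.9 × √0.64 = 22.32.
- With 96 evaluable per arm, SE = 22.32 × √(2/96) = 3.22.
- Expected z for each contrast, if both true differences are 10 points = 10/3.22 = 3.104.
- The contrasts share the wait-list arm. Their covariance is σ²/n and each variance is 2σ²/n, so the correlation is 0.5.
- Critical values: 2.241 (two-sided 2.5%) and 1.960 (two-sided 5%). Rejections in the wrong direction are negligible here.

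**3. Fixed split.**
- Per contrast: Φ(3.104 − 2.241) = 0.8058.
- Both: P(Z₁ > 2.241 and Z₂ > 2.241) = 0.6952.
- At least one: 2 × 0.8058 − 0.6952, about 0.916.

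**4. Holm.** P(Z₁ > 2.241 and Z₂ > 1.960) = 0.7402.
- Both: 2 × 0.7402 − 0.6952 = 0.7852, a gain of 9.0 percentage points.
- Per contrast: 0.8058 + (0.7402 − 0.6952) = 0.8508.
- At least one: unchanged, because the first step is the same test.

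A simulation of 400,000 trials with t statistics gave 69.1% and 78.2% for both.

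**5. Each contrast at an unadjusted 5%.** Power to show both is 0.793.

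**6. Family-wise error with both nulls true.** P(|Z₁| or |Z₂| exceeds the critical value), correlation 0.5:
- fixed split or Holm: 0.046;
- 5% each: 0.091.

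**7. Sensitivity of the power to show both.**

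| iEFT / iMMI true difference, evaluable per arm | Fixed split | Holm |
|---|---|---|
| 10 / 10, 96 | 69.5% | 78.5% |
| 10 / 7.5, 96 | 48.7% | 59.6% |
| 10 / 5, 96 | 23.4% | 32.7% |
| 10 / 12, 96 | 77.4% | 84.9% |
| 10 / 10, 113 (no drop-out) | 78.7% | 85.9% |

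If only one programme works, its power stays at about 80.6% to 80.7% under either rule. To match Holm's 78.5%, a fixed split would need about 113 evaluable per arm: 339 / 0.85 = 398.8, so about 399 randomised, 60 more than planned.

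**The case against.** A reader might infer that the protocol itself gives up 9 points of power. The article does not support that. The 2.5% level appears only as an input to the sample size, and no section says that the final tests use a fixed split. Sizing each contrast at half of alpha is also the usual conservative sizing for a Holm analysis, so Section 2.5 loses nothing and would keep its level under the fix.

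A reader might equally infer from Section 2.10 that each contrast will be tested at an unadjusted 5%. That is not stated either: 5% could be the level for the family, and Section 2.5 shows that the authors had the two comparisons in mind.

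Three further points carry weight.
- The 9 points concern success on both contrasts, a target the protocol never sets. Its target is 80% per contrast, and a fixed split meets it. The gain per contrast is about 4.5 points.
- Bonferroni is valid and has a real advantage: its simultaneous intervals always agree with its tests. Holm is also not the only improvement; a step-down Dunnett procedure would use the shared control.
- The article is a condensed account, and a statistical analysis plan that is not available here may already name a rule.

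These points limit the finding to an inexpensive improvement. They do not remove it, because the article prints two levels that do not meet, and each literal reading is worse than a rule that uses both.

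**Conclusion.** The point holds as a gap between planning and analysis that has a better method ready to hand. It is not an error in the sample size and does not threaten the trial's validity.

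Holm gives both printed levels a role: 2.5% for sizing and the first step, 5% for the second step and the family. Compared with a fixed split, it raises the chance of showing both programmes effective by about 9 points. Compared with 5% per contrast, it brings family-wise error under both nulls from about 9.1% to about 4.6% and gives up less than one point of power to show both (79.3% to 78.5%).

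The power figures assume the protocol's own inputs, a true 10-point difference for both programmes and 96 evaluable participants per arm. The gain is 7 to 11 points over the other scenarios in the table and practically nil if only one programme works.

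**What to change.** Keep the sample size at two-sided 2.5% per contrast. State in Sections 2.5 and 2.10, and in the statistical analysis plan, that the two primary T1 contrasts are tested by Holm at a family-wise two-sided 5%: the smaller p-value at 2.5% and, only if it is significant, the other at 5%. Report 97.5% intervals for both contrasts. If the analysis plan already names a valid rule, quote it in Section 2.10 so that the two levels agree.

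The cost is about one sentence in each place, with no extra participants, and it should be settled before the T1 data are analysed. The one downside is that the second contrast's 97.5% interval may include zero although Holm declares it significant. The report should say in advance that this can happen and why.
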